### Data Monitoring, Potential Harms, and Audit Process

HIV testing and HIVST at the workplace in Uganda are still novel and may result in unexpected harms and AEs. We set up a data safety and monitoring committee to oversee the progress of the trial. The committee is charged with ensuring that the trial protocol is adhered to and that the trial data are correctly recorded, analyzed, and reported. The trial quality-management officer, together with the research team, will monitor the participants for harm and AEs, such as physical violence, stigma, and discrimination at the workplace, as well as personal and social harm related to receiving HIV test results. AEs will be classified as mild, moderate, or severe. AEs such as suicide threats, self-harm threats, hospitalization, or death up to 28 days after a reactive HIVST result will be classified as severe [39]. The trial quality-management officer will report all events and withdrawals from the trial due to AEs using an open-ended AE reporting form. These data will be collected fortnightly. Severe events will be reported to the principal investigator and the Research Ethics Committee, while mild and moderate AEs will be recorded and reported to the trial counseling team. In the event of severe AEs, the data monitoring committee will evaluate the benefits and harms separately, followed by an overall measure that considers the balance between benefits and harms [40]. At the end of the trial, two independent officials will evaluate the trial-related activities and documents to ensure that they were carried out according to the protocol and Good Clinical Practices.

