### Ethics Approval, Trial Registration, and Informed Consent

Both the Makerere University School of Health Sciences Research Ethics Committee (reference No. 2018-054) and the Uganda National Council of Science and Technology (UNCST; reference No. HS 2672) granted ethics approval. The trial was registered at ClinicalTrials.gov (NCT04164433). Any important protocol deviations or adverse events (AEs) will immediately be communicated to the Research Ethics Committee, the UNCST, and ClinicalTrials.gov. Additionally, we will seek permission from the responsible personnel officer at every site.

Each participant will provide written consent prior to recruitment into the CRT and will receive a copy of the signed form. They will also be informed that their participation is voluntary and that they may withdraw from the study at any time. Furthermore, permission will be sought to audio-record and take notes during the interviews.

All disclosed HIV status results will remain confidential. The employers will be made aware that the results will remain confidential and that the workers are not under any obligation to disclose their results, especially in the event that this may lead to a loss of jobs for those who are found to be HIV positive. All original documents will be deposited in a secure locked cabinet and accessed only by the three investigators. The trial data set will not have any participant identifiers and will be stored in electronic password-protected files.

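### The only explicit severe-AE criterion is worded for a reactive self-test, so equivalent control-arm events (at least deaths) have no stated basis for severe grading or escalation

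*Protocol article*

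**What the plan says.** In *Data Monitoring, Potential Harms, and Audit Process* the protocol article builds its safety scheme in four steps.

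- **Scope.** The quality-management officer and the research team "will monitor the participants for harm and AEs, such as physical violence, stigma, and discrimination at the workplace", and also for personal and social harm linked to learning an HIV test result. No arm is singled out. The officer "will report all events and withdrawals from the trial due to AEs using an open-ended AE reporting form", with data gathered every two weeks.
- **Grading.** "AEs will be classified as mild, moderate, or severe". The article does not describe mild or moderate. For severe it gives one sentence, which opens with threats of suicide and of self-harm as examples and goes on: "hospitalization, or death up to 28 days after a reactive HIVST result will be classified as severe".
- **Routing.** The grade decides who is told: "Severe events will be reported to the principal investigator and the Research Ethics Committee, while mild and moderate AEs will be recorded" and passed to the counseling team.
- **Committee review.** When severe events occur, the data monitoring committee assesses benefits and harms and then their balance.

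*Ethics Approval, Trial Registration, and Informed Consent* sets a separate duty: "Any important protocol deviations or adverse events (AEs) will immediately be communicated to the Research Ethics Committee", and likewise to the national research council (UNCST) and the trial registry.

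**The concern.** The grade is not just a label. It decides whether the principal investigator and the ethics committee hear of an event, and whether the data monitoring committee weighs harm against benefit. A criterion that depends on a result only one arm can have lets like events be handled differently by arm.

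Two things are at stake. One is safety oversight of control men, who also receive HIV results and for whom the section itself foresees harm. The other is the committee's ability to read the severe events it sees in the self-test arm. Without control events graded by the same rule, it has no like-for-like background against which to judge them.

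**Working it through.** No figure in the plan depends on this point, so there is no calculation to reproduce. The check is a side-by-side reading.

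**1. Who can meet the trigger.** *Site Selection and Allocation* gives HIVST to the intervention clusters and standard testing to the control clusters. *Control Arm* specifies finger-stick rapid tests performed by a nurse or counselor. A reactive HIVST result therefore cannot come from trial testing in the control arm. *Sample Size Determination* plans 274 men per arm and 548 in all, so this concerns 274/548 = 50% of planned participants.

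**2. What the time-and-test qualifier governs.** The severe sentence lists four events and ends with the qualifier. The grammar allows three readings. For a control man they give:

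| Qualifier governs | Suicide or self-harm threat | Hospitalization | Death |
|---|---|---|---|
| the whole list | no stated grade | no stated grade | no stated grade |
| the last two items | severe | no stated grade | no stated grade |
| the last item only | severe | severe | no stated grade |

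The extent of the gap depends on the reading, but a control-arm death lacks a stated grade on all three. On the third, a control hospitalization would be severe while a control death would have no stated grade.

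**3. Whether the gap lies only between arms.** It does not. Intervention men with a nonreactive result, or with no result returned, are also outside the qualifier, as are events after day 28. *Intervention Arm* lets men test away from the study team, and *Discussion* concedes that confirming self-reported results will be a challenge. The trigger may therefore go unseen even where it exists.

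**4. From grade to route.** Severe leads to the investigator, the ethics committee and committee review. For the lower grades the stated route is that "mild and moderate AEs will be recorded and reported to the trial counseling team". An event with no stated grade has no stated route within this section.

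**5. The two reporting texts.**

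| | Ethics section | Monitoring section |
|---|---|---|
| Which events | important AEs (term not defined) | severe AEs |
| Recipients | ethics committee, UNCST, registry | principal investigator, ethics committee |
| Timing | immediate | fortnightly collection; no notification time given |

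The ethics committee is the only common recipient, and nothing links important to severe.

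**6. Use of the harm data.** *Statistical Analysis* compares uptake of testing, linkage to care and uptake of prevention services. It names no between-arm test of harms. The consequence is therefore limited to grading, escalation, and any count of severe events by arm.

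**The case against.** The strongest reply is that the sentence gives examples. It opens with a phrase that marks the list as illustrative, and the sentence before it grades all AEs without regard to arm. The section monitors all participants and has every event reported. Nowhere does it call a control-arm death mild or moderate. This stands as far as it goes: control events are left without a stated grade, and a sensible grader could call them severe. But the illustrative phrase widens the types of event. It does not clearly loosen the condition that follows a reactive HIVST result.

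A second reply is that the ethics section already sends important AEs to the ethics committee, whatever the arm or test. That is a real backstop. It does not assign a grade, and it names neither the principal investigator nor the data monitoring committee.

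Third, the two reporting texts can operate together. The monitoring section does not say that its recipients are the only ones, and fortnightly describes data collection, not a delay in notification. This also stands: the texts are unreconciled, not flatly contradictory.

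Fourth, this is a condensed article, and full grade definitions may sit in the full protocol. That disposes of any complaint about the undefined lower grades. It does not dispose of this point, because the severe criterion is stated here, and in terms specific to one arm.

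**Conclusion.** The point holds as a defect of wording with practical consequences. The one explicit criterion for severe is tied to a result that trial testing can produce only in the intervention arm, while the surrounding text covers everyone. Equivalent control events, at the least deaths, have no stated basis for a severe grade or for the escalation and committee review that follow from it. A severe-AE tally by arm under this wording would be asymmetric. The size of the asymmetry cannot be estimated, because the article gives no event rates.

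This rests on two assumptions: control men do not obtain a self-test outside the trial, and the clause is applied as written.

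Three stronger inferences are tempting, and the document does not support them:

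- **That no control event could ever be graded severe.** The clause says which events will be severe. It does not say that others cannot be.
- **That the harm comparison is biased against HIVST.** No such comparison is specified, and some intervention men fall outside the wording too.
- **That the 28 days, set against the 3-month follow-up, measure how much harm is missed.** *Linkage to Care or Prevention Services* sets those contacts to ascertain linkage, not as an AE observation window, so the ratio measures neither missed events nor bias.

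**What to change.** Reword the severe-AE criterion so that it applies identically in both arms, for example by tying it to any HIV test result instead of an HIVST result. Make clear which listed events the time limit governs, and state one common observation window, to be chosen by the sponsor. Tabulate severe AEs by arm on that basis. Reconcile the ethics and monitoring sections: say how important relates to severe, who receives which events, and how soon.

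The cost is a one-sentence amendment to the criterion, matching text on reporting, an updated AE form and slightly more events to report. The fortnightly collection already in place can carry it, and no sample-size figure or stated analysis changes. *Results* describes recruitment as ongoing when the article was submitted. Events already recorded would need to be regraded under the new wording so that both arms are counted alike.

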#### Intervention Arm

Since 2014, the WHO has encouraged countries to implement pilot HIVST programs to evaluate this approach. We will, therefore, follow the WHO strategy on self-testing to pilot HIVST in the workplace [22] (Figure 3). The strategy steps are as follows:

Explain the HIVST procedure and how to interpret the self-test results.Demonstrate the HIVST procedure and the interpretation of the results.Provide any additional instructional materials using an HIVST video.Answer any questions raised by the potential participant.Issue the OraQuick HIVST kits for collection of a mouth swab; participants will test at home or at a venue of their choice.Participants will return the results to the trial team in one of the following ways that will be agreed upon when they receive the kit:A phone call to the study toll-free line.A picture of the test results sent via email, WhatsApp, Facebook, or another preferred social media app.Presentation of the test kit at the health facility.Participant self-reporting the results at the health facility.Provide a referral slip and further information on linking to further services for those who receive a reactive self-test result. Those who test negative will receive further information and a referral to HIV prevention services.Provide participants with a counselor’s phone number. They will be offered the option of a call-back to return the results within 3 days of testing. Participants will also be told to use this number if they have any difficulty and need support during and after testing. This is in line with a recommendation from a study in Nigeria [36], where more than half of the participants who tested HIV positive used the helpline for support.Each participant will receive a code and instructions on what to write in case he is positive and can send these results as a text message. For example, 2018-7TR9-122-S is the code for a positive reactive test, and 2018-7TR9-122-T is the code for the nonreactive test. These codes will be randomly generated for each participant to avoid coworkers being able to accidentally interpret another person’s results.Participants who do not return the HIVST results within 3 days shall be phoned. This is in line with the Ugandan Ministry of Health test-and-treat strategy [6]. They will have given prior consent to be contacted.

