#### Control Arm

Security personnel allocated to the control arm will receive standard-of-care HIV counseling and testing based on the Ugandan Ministry of Health guidelines [6], as follows:

The control arm of this study will be offered standard facility-based care using antibody-based rapid diagnostic tests (RDTs), which follow the approved serial testing algorithm in Uganda for people above 18 months of age [6] (Figure 4).Whole blood will be collected via finger stick and capillary sampling by a trained HIV nurse or counselor who will use a lancet and transfer the blood to the screening test kit using a capillary tube. The specimen will be tested immediately.The nationally approved algorithm for HIV testing is as follows:All participants will undergo the screening test using the Alere Determine HIV-1/2 test (Abbott).All participants who receive a reactive result will undertake a confirmatory test using the HIV 1/2 STAT-PAK test (Chembio Diagnostic Systems).All participants with a nonreactive confirmatory test result will undertake a tie-breaker test using the SD BIOLINE HIV-1/2 test (Abbott).Participants whose samples react using the tie-breaker test shall be retested after 14 days.Participants who test positive will receive a referral slip to nearby public and private health facilities to expedite linkage to treatment, care, and support services.Participants who test negative will receive a referral slip for HIV prevention services. The participants will be referred to one of five public health facilities within the district.Each participant will be provided with a counselor’s contact number for continued consultation.

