### Linkage to Care or Prevention Services

The participants will be followed up at 1 month and 3 months to determine their linkage into prevention, treatment, or care.

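### Named harms are recorded on an open-ended form with no arm-neutral way of eliciting them described, so harm capture could differ between arms unless the fortnightly collection means real contact in both

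*Protocol article*

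**What the plan says.** **How harms are recorded.** Under *Data Monitoring, Potential Harms, and Audit Process*, the quality-management officer and the research team "will monitor the participants for harm and AEs, such as physical violence, stigma, and discrimination at the workplace", and for personal and social harm from receiving results. The officer is to report events, and withdrawals caused by them, "using an open-ended AE reporting form. These data will be collected fortnightly". No arm is singled out, and how an event comes to light is not described. Severe events lead the monitoring committee to weigh benefits against harms; mild and moderate events go to the counseling team.

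**Scheduled follow-up, both arms.** *Linkage to Care or Prevention Services* says: "The participants will be followed up at 1 month and 3 months to determine their linkage into prevention, treatment, or care". *Secondary Outcome Assessment* lists linkage, ART, circumcision, condom use and PrEP at those times. It mentions a questionnaire, which is not reproduced, and no harm item.

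**Other contact, self-testing arm.** Under *Intervention Arm*, results come back by phone, picture, coded text or at a facility. On the counselor's line: "They will be offered the option of a call-back to return the results within 3 days of testing". And: "Participants who do not return the HIVST results within 3 days shall be phoned".

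**Other contact, control arm.** Under *Control Arm*, men are tested face to face by a nurse or counselor, then receive a referral slip and a counselor's "contact number for continued consultation". The only later contact described is a 14-day retest for those with a reactive tie-breaker.

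**The concern.** An open-ended form records what reaches the person filling it in. If nobody puts the same questions to every man, an event is recorded only when he raises it or a conversation brings it out. The number of conversations then influences the count, and the two arms are not described as having the same number.

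The article itself gives reasons why a man might stay silent: fear of being labelled and doubts about confidentiality (*Background*), and possible job loss (*Ethics Approval, Trial Registration, and Informed Consent*).

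At stake is the committee's judgement on the balance of benefit and harm. With 274 men planned per arm, harm counts are likely to be small, and a handful of events found in one arm and missed in the other could tilt that judgement or the later account of safety.

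**Working it through.** **Step 1: the plan's own figures.** No figure is given for harms. The only number needed is the arm size. The continuity-corrected two-proportion formula (55% v 70%, two-sided 0.05, 80% power) gives 176 per arm, and 176 × 1.399 / 0.90 = 273.6, rounded up to 274. The stated 274 is reproduced and serves below only as a denominator.

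**Step 2: the two readings of fortnightly.**

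- *Collation of forms.* The scheduled contacts at which a harm could surface after testing are then the 1- and 3-month follow-ups in both arms. Self-testing men may have one or two more: result return, an optional call-back, or the call to non-returners.
- *Contact with every participant.* Three months is about 13 weeks, so about 6 contacts in each arm. The same one or two extras are added to a much larger shared base.

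**Step 3: illustration with assumed capture rates.** Assume the same true harm risk of 5% in both arms: 274 × 0.05 = 13.7 men per arm. Assume that 60-80% of events are captured under self-testing and 30-50% under control.

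- Self-testing: 13.7 × 0.6 = 8.2 to 13.7 × 0.8 = 11.0 recorded
- Control: 13.7 × 0.3 = 4.1 to 13.7 × 0.5 = 6.9 recorded
- Smallest ratio: 0.6 / 0.5 = 1.2
- Largest ratio: 0.8 / 0.3 = 2.7

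Pairing high with high (0.8 / 0.5 = 1.6) and low with low (0.6 / 0.3 = 2.0) gives a narrower range, but nothing in the document justifies that pairing. The 5% cancels from every ratio.

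**Step 4: illustration by number of contacts.** Let each contact detect an existing harm with probability q, independently. The proportion captured after k contacts is 1 − (1 − q)^k, and the spurious ratio is that quantity for self-testing divided by that for control. For q = 0.2, 2 v 4 contacts: (1 − 0.8^4) / (1 − 0.8^2) = 0.590 / 0.360 = 1.64.

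| q | 2 v 3 contacts | 2 v 4 | 6 v 7 | 6 v 8 |
|---|---|---|---|---|
| 0.2 | 1.36 | 1.64 | 1.07 | 1.13 |
| 0.5 | 1.17 | 1.25 | 1.01 | 1.01 |
| 0.8 | 1.03 | 1.04 | 1.00 | 1.00 |

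The smaller number is the control arm. The first two columns are the collation reading and the last two the contact reading. The model favors the concern: it assumes that the harm precedes every contact and that a result-return call elicits harm as well as a follow-up visit. The call-back and the non-return call come within days of testing and cannot find harms that arise later.

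**Step 5: what the checks show.** The imbalance matters only if fortnightly means collation and detection per contact is low. Asking a direct, identical question raises q, and down the table every ratio then moves toward 1.

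**The case against.** The strongest reply is that this article condenses a fuller protocol. The questionnaire and adverse event procedures are not shown, an open-ended form is a way of writing events down and not proof that nobody asks, and monitoring is described for participants in general. All of that stands, and it rules out several stronger readings that a reader might infer:

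- *That nothing is asked about harm at 1 and 3 months.* One can say only that no such item is described.
- *That fortnightly collection contradicts the follow-up schedule.* It does not: the 1- and 3-month visits are scheduled to establish linkage, and a fortnightly safety check could run beside them.
- *That every self-testing man gets extra calls.* The call-back is optional, the 3-day call goes only to non-returners, other return routes exist, and no text says that harm is raised in any of them.
- *That contact always favors the self-testing arm.* Control men meet a nurse or counselor at the test while self-testers may test at home, and both arms receive a counselor's number.
- *That a biased harm test is planned.* *Statistical Analysis* plans no between-arm comparison of harms, and the committee's weighing is triggered by severe events.

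Severe events are also worded around a reactive self-test result, which has no control-arm counterpart. That concerns classification, not how harms are found, and this point does not rest on it.

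What survives is narrower. The article commits to an open-ended instrument for harms it has already listed, leaves the meaning of fortnightly open, and describes different early contact in the two arms.

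**Conclusion.** The concern holds as a risk that the text leaves open, not as a demonstrated bias. If fortnightly means collation, harm capture can differ by arm and can affect the committee's benefit-harm judgement; if it means contact with men in both arms, little imbalance remains.

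The document does not determine the size. The 1.2 to 2.7 range rests wholly on assumed capture rates. The contact model, also on assumptions, gives 1.03 to 1.64 under collation and 1.00 to 1.13 under fortnightly contact. None of these is a prediction, and the direction is not certain.

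The change is worth making because it is cheap and helps under either reading. It does not touch the primary outcome.

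**What to change.** 1. At the existing 1- and 3-month contacts, put the same short closed checklist to every enrolled man in both arms: each harm already named in the data monitoring section, with yes/no, date and severity.
2. Base any between-arm statement on harms on these solicited answers, with all enrolled men as the denominator and the number not reached shown by arm.
3. Keep the open-ended form for volunteered events and expedited reporting, and present those separately.
4. State whether fortnightly means contacting participants or gathering completed forms, and that it applies equally to both arms.

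**Cost.** No new visits: a few more questions per interview, and more mild events on record. Enrollment began in February 2020 and follow-up is under way, so men already past a contact will have no solicited answer for it. They should be reported separately, by arm, and not counted as free of harm.
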